## Discussion

The practical need for trials such as this is evident and pressing. Millions of children around the world suffer from posttraumatic stress symptoms due to experiences of war and organized violence, and providing them with the most effective forms of evidence-based help is a crucial, global concern. As of yet, we still have limited evidence, especially from RCTs, on the effectiveness of interventions targeted at war-affected children. A standardized, manualized intervention like NET with wide applicability has the potential to become a very useful tool for providing help to such children, both in their original home countries and as immigrants, refugees or asylum seekers in other countries. Thus, providing evidence for its effectiveness in a variety of contexts makes for clinical research of great practical importance.

At the same time, even as CBT-based interventions seem to be effective in reducing PTSD symptomatology, we have no comprehensive view based on theory as to exactly how and in what conditions this happens. As such, the results of this trial may contribute significantly to our understanding of the mechanisms of change that are crucial to successful treatment of PTSD in children. The theory underlying NET suggests that improved contextualization of traumatic memories is central to recovery from PTSD, and thus we expect that improvements in the quality of traumatic memories will mediate its effectiveness. Results on the possible mediating role of decreased dysfunctional trauma-related cognitive appraisals in treatment effectiveness, as suggested by recent research [36,37], further contribute to the search for active mechanisms of change. Exploring the possible effects of treatment on elements of cognitive functioning will shed light on the relationships between level of cognitive performance, trauma and PTSD. Although a great variety of findings on cognitive impairment in PTSD exist, there is still significant disagreement as to which of these findings represent pre-trauma susceptibility and resiliency factors or effects of comorbid conditions and which toxic effects of trauma or PTSD [45-47].

Further, including exploration of the potential moderating effects of peri-traumatic dissociation, gender and level of cognitive performance on treatment effectiveness in this trial adds to its potential to help guide the future development of intervention methods.

### Generalizability of study results

As a pragmatic trial studying real-world effectiveness in a usual care setting, the contributions of this trial to assessing the practical usefulness and applicability of NET in Finland are direct and immediate. As effectiveness is studied directly in the healthcare system itself, there will be no need for a separate implementation and roll-out phase, should NET be found effective and applicable in this context. In addition, as no extra resources as such will be provided for participating units, successfully carrying out NET interventions during the study will be proof of the feasibility of using NET with current resource and time constraints in these units.

The results of this study will be generalizable to healthcare settings in the Nordic countries and most other high income countries where therapeutic interventions such as NET may be provided to immigrant children. The results will be less generalizable to care environments where healthcare services are organized in a very dissimilar manner or where significantly less resources are available for provision of healthcare.

### Risks and limitations

Though it is possible for participating children to temporarily experience increased stress and discomfort during NET sessions, long-term iatrogenic risks are not expected in this trial. However, interim analyses will be carried out to ensure NET is not performing worse than TAU to a clinically significant extent.

One notable challenge in this trial will be the question of language. The majority of therapeutic work carried out in this trial will likely take place with the help of interpreters. Whenever possible, the same interpreter will work with the same child in all NET or TAU sessions, and interpreters will be given instructions to work as literally as possible. Constant cooperation with the organization providing interpreters will be maintained throughout the study to ensure recruitment of interpreters who are familiar with trauma and therapeutic methods in general, as well as with the special requirements of the NET method. Results from earlier NET studies seem to suggest no significant differences in outcomes between using and not using interpreters [29]. However, especially as we are dealing with a method placing great emphasis on narration and verbalization, the use of interpreters may pose a variety of practical problems and must be considered a possible source of confounding effects on study results.

Another challenge for the trial is its reliance on mostly child-evaluated measures. For many of the factors under study, other forms of reliable measures do not exist. In addition, as clinicians will act as assessors for the most part in this trial, the battery of measures and instruments has to be kept relatively simple and manageable in scope. In any case, for some measures, such as the qualities of traumatic memories, it can be expected that self-evaluations by, in particular, the youngest children taking part will also present potential sources of confounding effects.

The varied nature of the treatment-as-usual condition we are comparing NET to also poses challenges. On one hand, we have attempted to mitigate this problem by also including a waiting list condition, and by collecting information about the kind of TAU offered to each child. On the other hand, this variety in TAU is to be expected in a pragmatic framework and is a realistic reflection of the varied practices currently in use at the participating treatment units.

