### Research questions and hypotheses

This study will address the effectiveness of NET in treating trauma-related symptoms and improving resilience and cognitive performance. The mediating roles of trauma-related cognitive appraisals and memory functions on this effectiveness will also be studied, as well as several moderators potentially affecting recovery. Accordingly, the research questions are as follows.Does NET reduce a) posttraumatic stress disorder symptoms, b) depressive symptoms and/or c) psychological distress symptoms in children traumatized by war more effectively than a waiting list condition or treatment as usual? Does NET increase resilience or improve cognitive performance?The hypothesis is that NET is more effective in reducing PTSD, depressive and psychological distress symptoms as well as in increasing resilience and improving cognitive performance than TAU or a waiting list condition, to a statistically and clinically significant degree.What changes in the participants’ trauma-related memory functions and cognitions can be observed as a result of NET treatment, as compared to a waiting list condition and treatment as usual?The hypotheses are that statistically significant differences between the NET group and the control groups will be found in the participants’ trauma-related memory functions and cognitions at the end of treatment. It is hypothesized that at the end of treatment, NET participants will show lower levels of overgeneralization and fragmentation in their autobiographical memories, as compared to baseline, as well as more spatial and temporal contextualization and coherence. The trauma memories of children after NET are expected to be less biased and intrusive as compared to controls, and include more verbal and fewer sensory elements. Finally, it is hypothesized that participants in the NET group exhibit greater reductions in dysfunctional trauma-related cognitive appraisals, as compared to the waiting list and TAU groups.To what extent do these changes in trauma-related memory functions and cognitions mediate the effectiveness of NET in reducing PTSD symptoms, depressive symptoms and psychological distress symptoms, increasing resilience and improving cognitive performance?The hypothesis is that beneficial changes in autobiographical memory, trauma-related memories and trauma-related cognitive appraisals partly explain the reduction in at least PTSD and depressive symptoms among children who participate in NET, and may contribute to increased resilience and improved cognitive performance.To what extent does level of peritraumatic dissociation, level of cognitive performance or gender moderate the effectiveness of NET in reducing trauma-related symptoms?The hypothesis is that participants with very high levels of peritraumatic dissociation benefit less from the intervention in terms of symptom reduction. Girls and children with higher levels of cognitive performance are hypothesized to benefit more from the intervention.

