### Procedure

A sequential procedure will be applied to data collection. Whenever a child is identified as a potential participant by a clinician at one of the co-operating units, information concerning the intervention and the related research is provided both to the participant him/herself and to his/her parents. If they are willing to participate in the research, informed consent will be requested from the child and his/her parents.

Waiting list control baseline data (T0) will be collected during this first meeting with the clinician. The children will then be randomly assigned to EITHER the ‘treatment as usual’ group (n = 40) OR the ‘NET intervention’ group (n = 40). Because of the treatment queues currently present at most of the treatment units, all participants will first be placed under waiting-list conditions for approximately three months (waiting list control condition, n = 80). In the unlikely case that there is no treatment queue at the moment, the participant will begin NET or TAU immediately and will not contribute waiting list control data.

At the start of the intervention or TAU, pre-test (T1) data will be collected from all participants. The T1 data will serve as an end measurement for the waiting list control condition and as the pre-test measurement for the NET intervention and the TAU control condition.

Data (T2) will also be collected once during the treatment for both the NET and the TAU groups. This will allow for proper analysis of mediating mechanisms. In the NET group, this assessment will take place at the time when the worst traumatic memories have been narrated.

Post-test data (T3) will be collected from participants in both groups, immediately after the intervention for the NET group, and after three months of treatment for the TAU group, and follow-up data (T4) will be collected during a joint family meeting, three months later.

In most cases, the clinician working as the therapist will also act as the assessor and collect data from the patients he/she is treating. In some cases, members of the research team may carry out some assessments, particularly for follow-up. Interpreters are used whenever needed during assessments, and will be present during all assessment and treatment sessions for children who are not fluent in Finnish.

The procedure will be continued until the sample size reaches the goal of n = 80, with data collection estimated to finish during 2017.

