#### Effect evaluation

The main effect of NET as compared to TAU and the waiting list control condition on the primary outcomes of PTSD symptom severity, depressive symptoms, psychological distress, resilience and cognitive performance will be analysed employing analyses of covariance. Potential confounding factors (age, gender, treating unit) will be included as covariates. The main effects of NET as compared to TAU and the waiting list condition on the secondary outcomes of trauma memory quality and trauma-related cognitions will be similarly analysed employing analyses of covariance. For all analyses of covariance, effect sizes will be reported as partial η^2^, with 95 % confidence intervals included.

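### Interpreter use is called a possible source of confounding but is missing from the ANCOVA covariates; adding it is a cheap, low-priority improvement

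*Protocol article*

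**What the plan says.** Three places in the protocol article bear on this point.

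- **Risks and limitations** states that "The majority of therapeutic work carried out in this trial will likely take place with the help of interpreters". It notes that NET relies heavily on narration, and concludes that "the use of interpreters may pose a variety of practical problems and must be considered a possible source of confounding effects on study results". The handling described there is operational: keeping the same interpreter for a child where possible, asking for literal interpreting, and recruiting interpreters familiar with trauma work.
- **Procedure** extends this to measurement. Interpreters "will be present during all assessment and treatment sessions for children who are not fluent in Finnish". T0 data are collected at the first meeting, before assignment, so interpreter need can be observed before allocation.
- **Effect evaluation** fixes the adjustment set: "Potential confounding factors (age, gender, treating unit) will be included as covariates". Nothing in the wording marks the list as open.

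Interpreter need is also not among the listed measures, is not a stated stratification factor under Randomization, and is not one of the three moderators (peritraumatic dissociation, cognitive performance, gender) in the research questions and the Discussion.

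**The concern.** The article names a factor as potentially confounding and then gives a list of potential confounders without it. By contrast, the other such source named in Risks and limitations, self-evaluation by the youngest children, is at least partly covered by the age covariate.

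The factor could matter in two ways. The outcomes are mostly child-reported, so for children not fluent in Finnish the answers pass through an interpreter in both arms. Interpreter need may also go with other prognostic features. If it predicts outcome, an unadjusted analysis leaves any chance difference between the arms in the NET-TAU estimate and leaves the related variation in the residual. With 40 per arm, such differences are not negligible.

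**Working it through.** **Inputs.** From the article: 40 children per arm, 1:1 allocation, and 52 participants required at alpha 0.05, power 0.80 and f of about 0.40. Assumed, because the article gives no figure: a proportion p = 0.5 to 0.8 of children needing an interpreter, and an outcome shift of 0.4 to 0.6 SD associated with that need.

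**1. The plan's own figure.** I used noncentral F power for a fixed-effects ANCOVA with numerator df 1 and noncentrality f² × N = 0.16 × 52 = 8.32. With two groups and one covariate this gives power 0.807 at N = 52, so the stated figure is reproduced.

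**2. Cost of one more covariate.** Age (1 df), gender (1 df) and treating unit (5 df, assuming six unit levels) make 7 covariate df. Adding interpreter need makes 8.

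| Setting | 7 df | 8 df |
|---|---|---|
| Power at N = 52, f = 0.40 | 0.8050 | 0.8045 |
| Power at N = 80, f = 0.40 | 0.9417 | 0.9416 |

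The required N stays at 52.

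**3. Chance imbalance between arms.** The SD of the difference in proportions is sqrt(2p(1-p)/40).

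- p = 0.5: 0.112, times 1.96 = 0.22
- p = 0.8: 0.089, times 1.96 = 0.18

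**4. Shift in the NET-TAU estimate (imbalance × effect).**

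- At the 95% limit: 0.18 × 0.4 = 0.07 SD to 0.22 × 0.6 = 0.13 SD.
- At a typical imbalance: the mean absolute difference is about 0.8 × SD, or 0.07 to 0.09. The shift is then 0.07 × 0.4 = 0.03 SD to 0.09 × 0.6 = 0.05 SD.
- With other assumptions (p from 0.5 to 0.9, effect 0.3 to 0.5 SD), the 95%-limit shift is 0.04 to 0.11 SD.

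For scale, the unadjusted SE of the NET-TAU difference is sqrt(2/40) = 0.22 SD. The largest shift above is 0.13/0.22, or about 0.6 SE.

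**5. Precision.** The share of outcome variance tied to interpreter need is p(1-p) × effect². This is 0.16 × 0.16 = 0.03 at the low end (p = 0.8, 0.4 SD) and 0.25 × 0.36 = 0.09 at the high end (p = 0.5, 0.6 SD). The SE would fall by about 1% to 5%, since sqrt(1 - 0.03) = 0.98 to 0.99 and sqrt(1 - 0.09) = 0.95. The gain is smaller if treating unit already absorbs part of it.

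**6. Effect by interpreter need.** The SE of the difference between the two stratum-specific effects is sqrt(2/(40p) + 2/(40(1-p))).

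- p = 0.5: sqrt(0.10 + 0.10) = 0.45 SD
- p = 0.8: sqrt(0.0625 + 0.25) = 0.56 SD

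Power to detect an interaction of 0.5 SD is 0.20 and 0.14 respectively. For 80% power the interaction would have to be about 1.25 to 1.57 SD.

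**The case against.** The strongest reply is that interpreter need is not a confounder of the randomized comparison. It exists before allocation, interpreters serve both arms, and randomization balances it in expectation. Chance imbalance is already part of what the test and confidence interval allow for. Risks and limitations uses the term loosely, and no section promises adjustment. The same section cites earlier NET studies as suggesting no difference in outcome with or without interpreters. Both inputs to the size calculation are assumed.

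Most of this stands. It removes any claim of systematic bias and makes the point small. It does not explain why a factor that the authors single out is absent from their own list of potential confounders, when it can be known at T0 and costs almost nothing to include. The article cites the earlier studies and still keeps the caution.

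Three stronger readings are tempting, and the article does not support them.

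- *The pooled NET-TAU result cannot be applied to interpreted or to direct care.* Generalizability of study results does not mention interpreters. It refers to high-income healthcare settings treating immigrant children. The average effect in that mixed caseload is a legitimate target for a pragmatic trial.
- *Interpreter need should be a fourth tested moderator.* The limitation's stress on narration makes a different NET effect plausible, but step 6 shows that a test with 80 children would resolve little.
- *The results will not show interpreter use at all.* Baseline comparisons between arms and the collection of wide biographical information are planned. Neither names interpreter use, and neither excludes it. Whether it is recorded at each visit is a detail that an article may leave to fuller documents.

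**Conclusion.** The mismatch is real: the article calls interpreter use a possible source of confounding, yet its stated covariates omit it. The consequence is modest. NET versus TAU is not systematically biased. The exposure is a chance shift of about 0.1 SD (0.07 to 0.13) at the 95% limit of imbalance, more typically 0.03 to 0.05 SD, plus a small loss of precision. These sizes rest on two assumptions that the article cannot confirm: that 50-80% of children need an interpreter, and that this need goes with a 0.4-0.6 SD difference in outcome. If need has no prognostic value, omitting it costs nothing. No stated figure in the plan changes. This is a low-priority improvement.

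**What to change.** - Record at T0, before the envelope is opened, whether the child needs an interpreter (yes/no).
- Add this variable to the covariates listed under Effect evaluation.
- Name it among the variables compared between arms at baseline, so that its balance is visible.
- If wanted, report the NET-TAU difference with its confidence interval by interpreter need, labelled descriptive, without adding it to the hypothesis-tested moderators.

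The cost is one extra field and one degree of freedom, spent on a factor whose prognostic value is unproven. The required sample size stays at 52 and the target of 80 is unaffected.

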## Conclusions

In summary, this article has described the rationale and design of a randomized controlled trial studying the effectiveness and prospective mechanisms of change of Narrative Exposure Therapy in the treatment of posttraumatic stress symptoms in children affected by war or armed conflict. Overall, the results of this trial will contribute to basic research on PTSD, memory processes and cognitive functions in children, as well as to applied research into therapeutic interventions and their development. Beyond the specific analyses described in this article, the data collected will be utilized in further interdisciplinary collaboration with researchers from the fields of political geography and social anthropology. In this context, qualitative analysis of the life stories resulting from NET is under consideration. We also hope to utilize the results of this study in future international comparative research, e.g., by exploring the effects of treatment location (country of origin vs. new home country) on the effectiveness of NET.

## Trial status

The trial started in December 2014 and data collection is expected to continue until 2017, with continuous participant enrolment.

## Abbreviations

C-PTCI: Children’s Post-Traumatic Cognitions Inventory
CBT: Cognitive-Behavioral Therapy
CRIES: Children’s Revised Impact of Event Scale
CSRS: Child Session Rating Scale
CYRM: Child and Youth Resilience Measure
DSRS: Depression Self-Rating Scale for Children
NET: Narrative Exposure Therapy
PDEQ: Peritraumatic Dissociative Experiences Questionnaire
PTSD: Posttraumatic Stress Disorder
RCT: Randomized Controlled Trial
RPM: Raven’s Progressive Matrices
SDQ: Strengths and Difficulties Questionnaire
SUDS: Subjective Units of Distress Scale
TAU: Treatment as usual
TF-CBT: Trauma-Focused Cognitive-Behavioral Therapy
TMT: Trail Making Test
TMQQ: Trauma Memory Quality Questionnaire
WMTB-C: Working Memory Test Battery for Children
